### 2.3. Procedure

#### 2.3.1. Recruitment and screening

The study will be conducted at the Altrecht Academic Anxiety Center. Individuals with PTSD symptoms will be approached by their therapists to participate in the current study. If written consent has been given, the research assistant may contact individuals directly as well. Those who are interested in participating will be invited for an appointment with one of the research assistants. During this appointment, the study will be explained and patients who wish to participate are asked to sign an informed consent-form. After consent, the Life Events Checklist for the DSM-5 (LEC-5) will be administered, along with a screening questionnaire assessing age, completed education, previously followed trauma-focused treatment, medication use, alcohol- and drug use, and suicidality. If patients report suicidal thoughts, suicidality risk will be assessed using the suicidality module of the MINI. If patients report a high risk of suicidality on the MINI., a senior therapist trained in the assessment of suicidality will make a final decision about the participation. By administering the Clinician-Administered PTSD Scale for DSM-5 (CAPS-5) and the screening questionnaire containing questions about the in- and exclusion criteria, it will be determined whether patients meet the criteria for participation.

#### 2.3.2. Randomization and allocation

After inclusion and the baseline assessment, participants will be randomly assigned to one of the three treatment conditions: EMDR therapy, EMDR 2.0, or the Flash technique, by means of permuted block randomization with block sizes of 3, 6 and 9 to be sure that group sizes are equal across conditions. Randomization will be performed by an independent researcher using an online tool. Stratified randomization will be performed with complex PTSD as stratification factor to ensure that patients with complex PTSD are equally distributed across conditions. There will be no blinding as participants and therapists will be able to tell which treatment arm they are allocated to. The CAPS-5 assessments, however, are conducted by assessors who are blind to the allocated treatment conditions.

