### 2.5. Sample size

To perform a power analysis for a multilevel model, it is required to estimate parameters based on earlier research (83), which was not possible for the interventions investigated in the current study. Power analyses were performed in G*Power 3.1.9.2, based on three pairwise comparisons between the conditions (EMDR therapy vs. EMDR 2.0, EMDR therapy vs. Flash, EMDR 2.0 vs. Flash) on the post-treatment measurement occasion. The power analysis is based on a two-sided *t*-test, in which two independent means will be compared with a Bonferroni-corrected alpha for the three pairwise comparisons = 0.0167 (0.05/3), power = 0.80 and Allocation ratio = 1. We aim to be able to detect a clinical meaningful difference between the conditions, what comes down to a medium to large effect size *d* = 0.65. To increase the power, we will include the baseline CAPS-5 score as a covariate in the analyses (84). By doing so, we expect to explain approximately a quarter of the variance at the post-treatment measurement. The residual variance reduces and gives us a sample size of *n* = 39 per condition, or *N* = 117 in total. To account for an expected 10% dropout, we will recruit a total 130 participants.

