### 2.6. Data analyses

The statistical analyses will be performed on an intention-to-treat basis. Pre-treatment group differences are assessed using one-way ANOVAs for continuous data and χ2 tests for categorical data. A multilevel model will be performed with Treatment Condition (EMDR therapy vs. EMDR 2.0 vs. Flash technique) and Time (weekly assessments during the treatment and bi-weekly assessments during the follow-up phase) as predictors in the model. Measurements are nested within participants. Multilevel models are preferred over a repeated-measures ANOVA as participants with missing data can be included. In Level 1 of the model, the outcome measures vary within participants over time. In Level 2 of the model, the intercepts and slopes of the growth trajectories vary between participants. All analyses will be performed using the statistical programs R (Version 4.2.2) and IBM SPSS (Version 28).

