#### 2.6.1. Aim 1: Treatment effectiveness

##### 2.6.1.1. Outcome measures CAPS-5, ITQ, and DES

To investigate the effectiveness of the three treatment conditions, the average scores will be estimated for the outcome variables at each time point for the three conditions. The baseline values will be included as covariate in the model. This will result in 3 (Condition: EMDR, EMDR 2.0, and Flash) × 2 (Time: T8 and T12) average score estimates. To investigate the differential effectiveness in reducing PTSD, complex PTSD and symptoms of dissociation of the treatments, these average score estimates will be compared across the three conditions. To answer the research question if the treatment arms are effective in reducing PTSD, complex PTSD, and symptoms of dissociation over time, the average scores of measurement occasions T0 vs. T8 and T0 vs. T12 will be compared using *t*-tests.

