##### 2.6.1.3. Moderation analyses

To investigate whether treatment effect is moderated by baseline characteristics (baseline CAPS-5, PCL-5, DES, BDI-II, AAQ-II scores, and CPTSD diagnosis), Condition × Time × Moderator interaction effects will be tested with the primary outcome measures (CAPS-5, ITQ, and PCL-5) as dependent variables.

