#### 2.6.2. Aim 2: Treatment efficiency

A survival analysis will be performed to investigate the efficiency of the interventions on symptom level. Estimates will be used to determine how much time is needed to reach a clinically significant change and a cut-off score on the PCL-5. Clinically significant change will be calculated by means of a Reliable Change Index (85). A cut-off score of 33 on the PCL-5 will be used, based on Bovin et al. (63) and Wortmann et al. (86). The estimates for the three treatment conditions will be compared using a log-rank test. A survival analysis is preferred since it accounts for censoring, which happens when not all participants reach a clinically significant change or the cut-off score during the course of the trial. Time will be defined by the amount of treatment sessions and ranges from one to six.

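### Complex PTSD stratifies the randomisation but is left out of the main between-arm analyses; adding it is a small, nearly free improvement

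*Protocol article*

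**What the plan says.** Allocation is by permuted blocks with one stratification factor: "Stratified randomization will be performed with complex PTSD as stratification factor". The stated purpose is "to ensure that patients with complex PTSD are equally distributed across conditions" (section 2.3.2).

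The between-arm analyses are described with named predictors:

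- Section 2.6, general model: "A multilevel model will be performed with Treatment Condition (EMDR therapy vs. EMDR 2.0 vs. Flash technique) and Time" as predictors.
- Section 2.6.1.1 (CAPS-5, ITQ, DES): "The baseline values will be included as covariate in the model". Section 2.6.1.2 repeats that sentence for PCL-5, BDI-II, BSI and AAQ-II. Neither section names another covariate.
- Section 2.6.2 (efficiency): "The estimates for the three treatment conditions will be compared using a log-rank test". No stratification is mentioned.
- Section 2.6.3 (acceptability): a one-way ANOVA with condition as the only independent variable.

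Complex PTSD does appear in section 2.6.1.3, on moderation, which states that for "baseline characteristics (baseline CAPS-5, PCL-5, DES, BDI-II, AAQ-II scores, and CPTSD diagnosis), Condition × Time × Moderator interaction effects will be tested". The outcomes of those models are the three primary measures: CAPS-5, ITQ and PCL-5.

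The sample size in section 2.5 counts baseline CAPS-5 as the only covariate.

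**The concern.** Blocked allocation within strata balances complex PTSD across the arms, so differences between patients with and without it largely drop out of the arm contrast. A model without the stratum still leaves that variation in its residual. The reported standard error then exceeds the true variability of the contrast: intervals are too wide and tests reject less often than their nominal level.

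Precision is at stake, not validity. The Discussion concedes that the trial cannot detect small differences between conditions, and section 2.5 presents covariate adjustment as a way to gain power. The one factor that determined allocation is an obvious candidate for the same treatment.

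**Working it through.** **Inputs from section 2.5.** "The power analysis is based on a two-sided *t*-test" with alpha 0.05/3 = 0.0167, power 0.80, d = 0.65, equal allocation, a quarter of the post-treatment variance explained by baseline CAPS-5, and 10% dropout.

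**Reproducing the plan's figure.** The noncentral t calculation without a covariate gives 52 per arm. With residual variance 1 − 0.25 = 0.75, this becomes 52 × 0.75 = 39 per arm. The total is 3 × 39 = 117, and 117 / 0.90 = 130. All three stated figures are reproduced without complex PTSD in the model. Power at 39 per arm is 0.804 (noncentrality 0.65/√0.75 × √(39/2) = 3.31).

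**Assumption.** Let q be the share of the variance left after baseline that complex PTSD explains. The article gives no value, so q is varied from 0 to 0.20.

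**Standard error.** With balanced strata the true standard error is proportional to √(0.75(1 − q)). The model without the stratum reports one proportional to √0.75. The ratio of reported to true is 1/√(1 − q).

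**Power and type I error.** Each q was simulated 40,000 times for one pairwise comparison: 39 per arm, stratum balanced across arms, complex PTSD assumed in about half of patients, true difference 0.65 or 0. Monte Carlo error is about √(0.8 × 0.2/40,000) = 0.002 for power and √(0.0167 × 0.9833/40,000) = 0.0006 for type I error.

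| q | Reported / true SE | Power without factor | Power with factor | Gain (points) | Type I error without factor |
|---|---|---|---|---|---|
| 0 | 1.000 | 0.807 | 0.807 | 0 | 0.016 |
| 0.02 | 1.010 | 0.807 | 0.814 | 0.7 | 0.016 |
| 0.05 | 1.026 | 0.811 | 0.828 | 1.7 | 0.0145 |
| 0.10 | 1.054 | 0.816 | 0.849 | 3.3 | 0.011 |
| 0.20 | 1.118 | 0.827 | 0.892 | 6.5 | 0.008 |

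The noncentral t formula with residual variance 0.75(1 − q) agrees for the model with the factor: 0.804, 0.813, 0.827, 0.849 and 0.893. The number per arm needed for 80% power with the factor is 39, 38, 37, 35 and 32.

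Both power columns must be read along the same row. Setting the planned 0.80 (q = 0) against 0.83 or 0.85 (q = 0.05 or 0.10, factor included) mixes two scenarios and overstates the gain.

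**The case against.** The case against acting has four parts.

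1. *A reader might infer that no model of an efficacy outcome contains the factor.* That is wrong: section 2.6.1.3 puts complex PTSD diagnosis into models for all three primary measures. Those models test whether the treatment effect differs by complex PTSD, however. They do not adjust the main comparison, so the point survives in narrower form.

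2. *The loss may be close to nothing.* Section 2.4.1.3 assigns the diagnosis of complex PTSD to the ITQ, so the baseline ITQ score in the ITQ model probably carries much of the stratum information. Baseline CAPS-5 may carry some too. This stands, and it is why the range has to start at q = 0. It does not extend to the log-rank test or the acceptability ANOVA, which have no baseline covariate. Equally, nothing in the article shows that complex PTSD predicts those two outcomes, and no size is calculated for them here.

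3. *The plan already meets its target.* This stands in full. The 39 per arm was derived without the factor, and power without it is about 0.80 or higher in every row of the table.

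4. *A condensed article leaves covariate lists to the full protocol or SAP.* That is possible, and either may name the factor. But this article does list its covariates and gives the reason for adjusting, so the models as written omit the stratum. They do not say that it is excluded, and this is no contradiction within the document.

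**Conclusion.** The point holds as a minor matter of efficiency and alignment. The trial randomises by complex PTSD, and its main between-arm analyses as described do not use it. At an assumed 2% to 10% of residual variance explained, standard errors are about 1% to 5.4% too wide and about 1 to 3 points of power are forgone. At zero there is no loss.

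Two stronger readings are not supported. One is that the trial is underpowered because of the omission: the planned 80% does not rest on this factor. The other is that the omission makes the tests invalid: actual type I error is at or below the nominal 0.0167, and balanced allocation leaves the contrast unbiased.

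The figures depend on the assumed q, on balance within strata, on about half of patients having complex PTSD, and on section 2.5's own inputs.

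**What to change.** Add the randomisation stratum (complex PTSD yes/no, as used for allocation) as a fixed effect in the main between-arm models for CAPS-5, ITQ, DES, PCL-5, BDI-II, BSI and AAQ-II. For consistency, include it in the acceptability comparison and stratify the log-rank test by it. The moderation analyses can stay as they are. If an unseen SAP already does this, a sentence in section 2.6 saying so is enough.

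The cost is one degree of freedom per model and no new data, since the factor is known before allocation. State it before outcomes are examined by arm, so that the choice of adjustment cannot look driven by the results.

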#### 2.3.3. Assessments

At baseline assessment (T0), the CAPS-5 will be administered by a trained therapist, along with the Life Events Checklist for DSM-5 (LEC-5). The International Trauma Questionnaire (ITQ), PTSD Checklist for DSM-5 (PCL-5), Dissociative Experiences Scale (DES), Beck Depression Inventory-II (BDI-II), Brief Symptom Inventory (BSI), and the Acceptance and Action Questionnaire-II (AAQ-II) will be administered digitally. The baseline assessment takes approximately 90 min. After the baseline assessment and the session where the treatment plan is drawn up, a 6-week treatment phase commences during which participants fill out questionnaires weekly prior to the treatment sessions (T1-6). Questionnaires include the PCL-5, BDI-II, BSI, and AAQ-II and take approximately 30 min in total to complete. After the first treatment session (T2), a questionnaire about treatment acceptability is administered. After the treatment phase, a 12-week phase commences where no actual treatment is delivered, but participants fill out the PCL-5, BDI-II, BSI, and AAQ-II bi-weekly (T7-12). The treatment acceptability questionnaire is administered again at T7. The CAPS-5, ITQ, and DES are administered 4 weeks after treatment is completed (T8), and 12 weeks after termination of treatment (T12). To minimize missing data, reminders will be sent out to the participants to fill out the questionnaires. For a complete overview of the timing of the interventions and assessments, see Figure 1.

**FIGURE 1 F1:**
[figure not shown]
SPIRIT timeframe of the study. From T1 to T6, the measurements take place weekly. From T7 to T12, the measurements take place bi-weekly.

### 2.4. Instruments

#### 2.4.1. Primary outcome measures

The primary study outcomes are severity of (complex) PTSD symptoms and PTSD diagnosis which are measured with several instruments.

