**Methods:**

A total of 130 patients diagnosed with (complex) PTSD will be randomly allocated to either six sessions of EMDR therapy, EMDR 2.0, or the Flash technique. The primary outcomes used to determine treatment effectiveness include the presence of a PTSD diagnosis and the severity of PTSD symptoms. The secondary outcomes of effectiveness include symptoms of depression, symptoms of dissociation, general psychiatric symptoms, and experiential avoidance. All patients will be assessed at baseline, at 4-week post-treatment, and at 12-week follow-up. Questionnaires indexing symptoms of PTSD, depression, general psychopathology, and experiential avoidance will also be assessed weekly during treatment and bi-weekly after treatment, until the 12-week follow-up. Efficiency will be assessed by investigating the time it takes both to lose the diagnostic status of PTSD, and to achieve reliable change in PTSD symptoms. Treatment acceptability will be assessed after the first treatment session and after treatment termination.

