##### 2.6.1.2. Outcome measures PCL-5, BDI-II, BSI, and AAQ-II

For the outcome measures administered (bi)-weekly, a multilevel model will be performed. The baseline values will be included as covariate in the model. It will be investigated if the treatment conditions are effective in reducing self-reported PTSD symptoms (PCL-5), comorbid symptoms (BDI-II and BSI) and experiential avoidance (AAQ-II) over time. To investigate the differential effectiveness of the treatments, a Time × Condition interaction will be tested with the outcome measures as dependent variables. To investigate the effectiveness of the treatments, the effect of time will be tested with the outcome measures as dependent variables.

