There are some limitations of the study design that need to be addressed. First, a limitation includes the risk of missing data, due to numerous measurement occasions after the treatment phase. However, by using a statistical method that handles missing data well, we mitigate the impact of missing data on the statistical power. Furthermore, a limitation of the present study is that the participants are not blinded to their treatment conditions. This makes the design susceptible to expectancy effects of the participants. However, we do not anticipate that these expectancy effects will be stronger for one condition than for another, and the randomization process should account for an even distribution if these effects would occur. Another limitation is the absence of an inactive control condition. To this end, on the one hand, our study is a suboptimal design for testing the hypotheses that the experimental conditions are effective treatments for PTSD. In contrast, the active control condition in this study has been frequently compared to wait-list control conditions (7, 8), showing that EMDR therapy was more effective in the treatment of PTSD than wait-list control conditions. Therefore, we can assume that when EMDR 2.0 and the Flash technique have comparable effect sizes in comparison with EMDR therapy, these interventions are likely to be more effective than a waitlist control condition in the treatment of PTSD. Finally, a limitation of the present study is that the design and sample size will not yield enough statistical power to detect small effect sizes when comparing the treatment conditions or when investigating moderators of effectiveness.

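### CAPS-5, ITQ, PCL-5 and PTSD diagnosis are all primary, two of them compared at two visits, but the 0.0167 alpha and 80% power cover three comparisons at one visit

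*Protocol article*

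**What the plan says.** **Which outcomes are primary.** The abstract: "The primary outcomes used to determine treatment effectiveness include the presence of a PTSD diagnosis and the severity of PTSD symptoms". Section 2.4.1: "The primary study outcomes are severity of (complex) PTSD symptoms and PTSD diagnosis which are measured with several instruments", followed by CAPS-5, PCL-5 and ITQ. Section 2.6.1.3 refers to "the primary outcome measures (CAPS-5, ITQ, and PCL-5) as dependent variables". None is ranked above another.

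**How they are compared.** For CAPS-5 and ITQ (and the secondary DES), section 2.6.1.1 produces "3 (Condition: EMDR, EMDR 2.0, and Flash) × 2 (Time: T8 and T12) average score estimates" and compares these across the arms, with neither visit preferred. For PCL-5, section 2.6.1.2 says that "a Time × Condition interaction will be tested with the outcome measures as dependent variables". Section 1.4 promises a comparison of the arms on loss of PTSD diagnosis, but section 2.6.1 describes analyses of scores only.

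**What the trial is sized for.** Section 2.5 uses a two-sided t-test at the post-treatment occasion with a "Bonferroni-corrected alpha for the three pairwise comparisons = 0.0167 (0.05/3"), power 0.80, d = 0.65 and the baseline CAPS-5 score as covariate, expected to explain about a quarter of the variance. The result is 39 per arm, 117 in total and 130 with 10% dropout.

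**The concern.** Dividing 0.05 by three accounts for the arm pairs on one score at one visit. The declared primary set is wider: three instruments and a diagnosis, two of the instruments compared at two visits. The plan does not say whether success means a difference on any primary measure, on all of them, or on a particular one.

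That gap decides what the trial can claim. With no rule, a difference between two arms on any primary measure at either visit could be reported as the primary result, each with its own chance of being a false positive. If the authors correct for this afterwards, the power falls below the figure used to justify the sample size. A reader of the results could not tell which contrast carried the confirmatory claim. For diagnosis, the article gives a primary outcome with no described comparison between arms.

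**Working it through.** **1. Reproduce the plan's figure.** Inputs from section 2.5: d = 0.65, 25% of variance explained, two-sided alpha 0.05/3, power 0.80, equal arms.

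- Effective difference: 0.65/√(1 − 0.25) = 0.7506.
- At n = 39 per arm the noncentrality is 0.7506 × √(39/2) = 3.314. The critical t on 76 degrees of freedom is 2.448.
- Power from the noncentral t is 80.4% at n = 39 and 79.2% at n = 38, so 39 is correct.
- 3 × 39 = 117, and 117/0.9 = 130.

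The arithmetic is right. The question is which tests it covers.

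**2. Count the documented primary contrasts.** Section 2.6.1.1 gives 2 primary instruments (CAPS-5, ITQ) × 2 visits (T8, T12) × 3 pairs = 12. PCL-5 adds one Time × Condition interaction under section 2.6.1.2. Diagnosis adds no described test. The figures below use the 12 only.

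**3. Family-wise error at 0.05/3 per test, no true differences, any significant contrast counted as success.**

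- Union bound: 12 × 0.05/3 = 20%.
- Simulation: three arm means, pairwise differences, two-sided normal threshold at 0.05/3, four correlated endpoints (two instruments × two visits). The document gives no correlations, so they are assumed. In the equal structure every pair of endpoints has the same correlation r. In the product structure r applies between instruments and between visits, and r² when both differ.

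| Assumed r | One score, one visit (3 tests) | CAPS-5 at T8 and T12 (6 tests) | CAPS-5 and ITQ at both visits (12 tests): equal / product |
|---|---|---|---|
| 0 | 4.4% | 8.6% | 16.5% / 16.5% |
| 0.6 | 4.4% | 7.8% | 13.2% / 13.7% |
| 0.8 | 4.4% | 7.1% | 10.5% / 11.0% |
| 0.9 | 4.4% | 6.3% | 8.6% / 9.0% |

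Over correlations of 0.6–0.8 the 12 contrasts give about 11–14%. Even at 0.9 the error stays well above 5%. The three-test family that the plan corrects for is controlled, at 4.4%.

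**4. Power if the correction is widened to the 12.** Alpha is 0.05/12 = 0.00417. With the same effective difference and n = 39, power per comparison is 64.0%. Restoring 80% needs 51 per arm: 153 in total, or 153/0.9 = 170 recruited. This assumes the same d and variance explained for each score and visit.

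**5. If all four scores must be significant for a given pair.** False positives are then controlled. With the full d = 0.65 on every score, power at n = 39 is about 58–67% over correlations of 0.6–0.8.

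**6. Summary by decision rule.**

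- *Any, uncorrected:* the error rate exceeds 5%.
- *Any, corrected:* power per comparison is about 64%.
- *All:* power is about 58–67%.
- *One named score at one visit:* 5% and 80% both hold.

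**The case against.** **The analysis alpha and multiplicity rules may sit in an analysis plan not shown.** This is fair. The 0.0167 appears only in the sample-size section, and sections 2.6 to 2.6.1.3 state no alpha. But the primary set and the alpha used for sizing are both fixed in this article, and they do not match. A later plan can resolve that only by narrowing the set, ranking it, or accepting lower power.

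**The powered contrast can already be identified.** The abstract calls the 4-week visit post-treatment and the 12-week visit follow-up, section 2.5 adjusts for baseline CAPS-5, and section 2.4.1.1 treats CAPS-5 as the reference instrument. This stands as inference, and it is why the fix is cheap. It is not a designation: section 2.5 does not name the powered outcome.

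**Power does not fall merely because other outcomes exist.** Correct. A reader might infer that 80% power applies to just one of the primary tests. It does not: the calculation already covers three pairwise comparisons, and it gives the same power per comparison for any continuous score and visit with d = 0.65 and 25% of variance explained. Under an any-outcome rule the chance of finding at least one effect exceeds 80%. Power is lost only if a wider correction is applied or all outcomes must succeed.

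**Larger counts are tempting.** Three instruments × two visits × three pairs makes 18 tests, but PCL-5 has an interaction test, not pairwise contrasts at T8 and T12. Error rates at 0.05 per test would assume that the stated correction is dropped at analysis, and nothing in the article says so.

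**Open allocation.** A reader might add that self-reported primaries are exposed to expectancy, because the Discussion says "the randomization process should account for an even distribution if these effects would occur". That sentence governs no analysis, and the same paragraph already lists the lack of blinding as a limitation. It is a separate matter from multiplicity.

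**Conclusion.** The point holds. The sample-size arithmetic is correct, but it covers a narrower family than the declared primary outcomes. Under an any-contrast rule at 0.0167, the 12 documented CAPS-5 and ITQ contrasts carry a family-wise error of about 11–14% instead of at most 5%. Bonferroni over the 12 leaves about 64% power per comparison instead of 80%. Separately, PTSD diagnosis is called primary while section 2.6.1 describes no comparison of it between arms.

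This rests on four assumptions: correlations of 0.6–0.8, which the document does not give; the same d and variance explained for each score and visit; the 0.0167 of section 2.5 carried into the analysis; and the inference that the powered outcome is CAPS-5. The article does not label T8 and T12 as primary visits; it analyses primary measures at both and singles out neither. Which guarantee fails depends on the unstated decision rule, but under none of the any or all rules do 5% and 80% both hold for the whole set.

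**What to change.** Name CAPS-5 total severity at T8, rated by the blinded assessors, as the single primary endpoint. Test its three pairwise contrasts at 0.0167 each, or by Holm at an overall 0.05. Make ITQ, PCL-5, PTSD diagnosis and all T12 results secondary, and state how diagnosis will be compared between arms. Amend the abstract and sections 2.4.1, 2.5 and 2.6.1 so that they name the same endpoint and visit, and update the registry entry.

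The stated 39 per arm, 117 in total and 130 recruited then match the primary claim, and no further data are needed. The cost is that the other measures lose primary status, including the complex-PTSD measure and diagnosis. The amendment must be made and dated before outcome data are examined.

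A pre-specified hierarchy would also repair the mismatch, as would a wider correction with a new sample size. Bonferroni over the 12 contrasts would mean about 170 recruited instead of 130.
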